## Methods

### Design

This study is a cluster randomised controlled trial (RCT) to test the efficacy of an intervention, i.e., a clinician's referral to a physical activity program, to generate a) behaviour change (i.e., increasing physical activity levels) that is sustained over time and b) improved psychological well-being, quality of life, and objective physical functioning outcomes among prostate cancer survivors. The potential influence of individual and environmental mediators on participation in physical activity will also be determined.

Clinicians who agree to be involved in the study will be randomized into the intervention or control condition prior to the commencement of the study via computer-generated table of random numbers. Blinding of the clinician is not possible in this study, as one of our aims is to assess if the referral to the physical activity program by clinicians' influences the uptake of the physical activity program.

Our decision to undertake a cluster RCT, randomised by clinician with no cross over, was one based on the pragmatics of our situation. Our previous experience in this field suggests that it is difficult to gain support from busy clinicians if they were required to switch between both experimental conditions in the recruitment of patients [22]. Therefore, clinicians will be randomised into one of the two conditions and patients of each clinician will be regarded as separate clusters. There are likely to be up to twelve clinicians involved in this study (three clinicians from each of the three health services). Although we anticipate the effect of variation in the health services and in clinician physical activity recommendations on the key outcomes of this research to be very small, possible differences need to be taken into account through the use of clustering [23].

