**Methods/Design:**

This study is a cluster randomised controlled trial. Clinicians of prostate cancer survivors will be randomised into either the intervention or control condition. Clinicians in the intervention condition will refer eligible patients (n = 110) to participate in an exercise program, comprising 12 weeks of supervised exercise sessions and unsupervised physical activity. Clinicians allocated to the control condition will provide usual care to eligible patients (n = 110), which does not involve the recommendation of the physical activity program. Participants will be assessed at baseline, 12 weeks, 6 months, and 12 months on physical activity, quality of life, anxiety, depression, self-efficacy, outcome expectations, goals, and socio-structural factors.

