### Participants

Eligible patients will be adult males who 1) have completed active treatment for prostate cancer within the previous three-12 months. Participants currently on hormone treatment will be eligible to participate; 2) were treated with curative intent, representing stages I, II, or III; and (3) have the ability to complete surveys in the English language. Patients will be excluded from this study if they have musculoskeletal, cardiovascular, or neurological disorders that could limit them from exercising. The patients' treating clinicians will assess their eligibility for the study.

The sample size for this study was calculated based on the primary research question; number of minutes of moderate or strenuous physical activity in a typical week in past month as measured by an adapted version of the Leisure Time Exercise Questionnaire at the completion of the 12 week intervention using the following assumptions: (1) a medium-sized effect will be found, (2) α will be set at .05, (3) power will be set at .80, (4) the attrition rate will be 10% at 12 weeks, and (5) the design effect will be 1.084. The anticipated effect size was judged from a similar project [24], where a medium-sized effect was found for the outcome of a physical activity intervention (*d *= 0.484), where the intervention group increase their total weekly minutes of physical activity by 59.3 minutes (SD = 126.6).

Physical activity levels will be measured at 12 weeks to answer the primary research question. An attrition rate of 10% is expected, based on our previous work in this area [22]. A design effect of 1.084 was included to account for clustering (ICC = .005, *m¯¬ *= 16.83). The ICC was estimated from a recently completed study investigating recruitment of newly diagnosed prostate and colorectal cancer patients (clustered by specialist) [22] and from published commentary in which the authors suggested that ICC rates of less than 0.01 have been found for practitioner prescribing rates [23]. The average size of each cluster (*m¯*) was calculated from an estimation of the number of participants needed in this study before the application of the design effect (*n *= 202) and the number of clinicians (clusters) involved in this research (*n *= 12). Based on these assumptions, 220 participants will need to be recruited.

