### Procedures

Following ethical review and approval, we will invite clinicians from three healthcare settings to participate in the study. Clinicians will be randomly allocated to either the intervention or control conditions and trained prior to commencement of the study in the study's objectives and clinician requirements including the referral process, requested dialogue and documentation completion. Adherence to the intervention and control groups' processes, will be monitored weekly by the project manager.

Eligible patients will be identified by the health service oncology nurses prior to presentation to either the public health service outpatient clinic or private health service rooms for their follow up consultation. During clinic sessions, members of the research team will approach eligible patients and introduce the study to the patient, provide an information package and seek verbal approval to follow them up within 48 hours regarding their interest in participating in the study.

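### Nine to twelve clinicians in three health services are randomised with no stratification by service described, so arm and service may be partly confounded; the likely harm is modest and the remedy is cheap.

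*Protocol article*

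**What the plan says.** The Design section of the protocol article states that clinicians will be "randomized into the intervention or control condition prior to the commencement of the study via computer-generated table of random numbers". The Procedures section adds only this: "Clinicians will be randomly allocated to either the intervention or control conditions and trained prior to commencement of the study". Neither place, nor any other, mentions stratification, blocking, matching or a fixed number of clinicians per arm. Neither says that allocation is unrestricted.

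The number of units is small and not settled. The Design section expects "up to twelve clinicians involved in this study (three clinicians from each of the three health services", which multiplies to nine; the sample size paragraph under Participants uses 12.

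The Design section expects the effect of variation between health services and clinicians to be very small, but still says that "possible differences need to be taken into account through the use of clustering". The cluster is the clinician. The Analysis section names an ANCOVA on 12-week activity with the baseline score as covariate and no term for service. The abstract plans 110 patients per arm.

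**The concern.** With so few units, chance can place all the clinicians of one service in the same arm. Any outcome difference between that service and the others is then mixed with the intervention effect. The authors acknowledge that service differences should be taken into account, but the device they name does not do it. Treating each clinician's patients as a cluster allows for correlation within a clinician's list; it neither spreads services across the arms nor removes a service effect. The named ANCOVA has no service term either.

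A second, smaller matter is the split of clinicians between arms. An uneven split costs power, or requires some clinicians to recruit many more patients than others to reach 110 per arm.

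**Working it through.** **Inputs from the article.** Three services; 9 or 12 clinicians, taken as 3×3 or 3×4; ICC 0.005; design effect 1.084; d = 0.484; SD 126.6 min/week; planned difference 59.3 min/week; 220 recruited; 10% attrition, so 198 analysed. **Assumed:** two-sided α of 0.05 and equal cluster sizes.

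**The plan's own figure.** The article gives no figure for allocation balance. Its sample size matters here because it sets the power margin. With d = 0.484 and 80% power, 68 per arm are needed, 136 in total; 136/0.9 gives 152, and applying the design effect to 136/0.9 gives about 164, not 220. The stated 202 and 220 are reached at about 90% power (91 per arm, 182 in total; 182/0.9 ≈ 202; ×1.084 ≈ 219). So 220 patients carry more power than the stated 0.80.

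**Chance that at least one service falls wholly in one arm**

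*Independent 1:1 draws.* A service of three is unmixed with probability 2 × (1/2)³ = 1/4, so 1 − (3/4)³ = 57.8%. A service of four is unmixed with probability 1/8, so 1 − (7/8)³ = 33.0%.

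*Equal arms forced, no stratification.*
- 3×4, split 6:6, 924 allocations. One given service wholly in one given arm: C(8,2) = 28 ways; × 3 services × 2 arms = 168. Subtract the allocations counted twice, with one service wholly in each arm: 6 ordered pairs × C(4,2) = 36. This leaves 132/924 = 14.3%.
- 3×3, five in one arm, 126 allocations. 3 × [C(6,2) + C(6,5)] = 63; subtract 6 × C(3,2) = 18. This leaves 45/126 = 35.7%.

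*Stratified by service.* 0%.

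**Effect on the estimate.** Standard error on the plan's inputs, without credit for baseline adjustment: 126.6 × √(4 × 1.084/198) = 18.7 min/week. For the service effect, assign the whole ICC of 0.005 to the service level. The service SD is then 126.6 × √0.005 = 8.95. The chance shift in the estimate has SD 8.95 × √(mean of Σ(p₁ₛ − p₀ₛ)²), where p₁ₛ and p₀ₛ are the shares of each arm's clinicians that come from service s. Averaging over every possible allocation (leaving out the two with an empty arm):

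| Allocation | 3×3 | 3×4 |
|---|---|---|
| Independent draws | 5.6 | 4.7 |
| Equal arms only | 5.2 | 4.4 |
| Stratified, arms within one clinician | 3.3 | 0 |

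For the 3×3 layout the total standard error is √(18.7² + 5.6²) = 19.5 under independent draws and √(18.7² + 3.3²) = 19.0 under stratification, a gain of under 3%.

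**Unequal splits, if draws are independent.** Power uses 220 patients, 10% attrition, d = 0.484 and ICC 0.005, with patients following clinicians.

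| Clinicians | Split | Chance of this or worse | Power |
|---|---|---|---|
| 12 | 6:6 | – | 0.907 |
| 12 | 8:4 | 38.8% | 0.871 |
| 12 | 9:3 | 14.6% | 0.811 |
| 12 | 10:2 | 3.9% | 0.686 |
| 9 | 5:4 | – | 0.896 |
| 9 | 6:3 | 50.8% | 0.863 |
| 9 | 7:2 | 18.0% | 0.768 |

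Had the trial been sized for exactly 0.80 at an equal split, 8:4 or 6:3 would give 0.752.

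**The case against.** A reader might infer that the plan prescribes simple, unrestricted randomisation and that the arms will be badly unequal. The text does not establish either. A table of random numbers can serve simple, blocked or stratified lists, the article condenses a fuller protocol that is not shown, and 110 patients per arm suggests that an equal split was intended. This stands. The 58% and 33%, and the table of unequal splits, are therefore conditional on independent draws. It does not dispose of the point, because equal arms alone still leave 36% or 14%; only restriction by service removes the risk.

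A reader might also infer serious bias or an underpowered trial. The article's own expectation is that service effects are very small. Patients of one clinician share a service, so a service-level correlation well above 0.005 would conflict with the clinician-level ICC used for the sample size. Baseline adjustment should also remove part of any stable difference between services in activity. These arguments stand, and they limit the size of the harm.

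Finally, stratifying puts both arms in every service, where oncology nurses identify patients, so contamination could rise. Under independent draws all three services are mixed in 0.75³ = 42% (3×3) or 0.875³ = 67% (3×4) of draws; stratifying makes this 100%. That is a real but limited trade-off, because randomising by clinician already accepts both arms within a service.

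**Conclusion.** The point holds as a cheap improvement, not as a demonstrated flaw. The article describes no restriction by service for 9 to 12 randomised clinicians, and neither the clustering nor the named ANCOVA deals with the service differences it says should be taken into account. The reason to act is the possible confounding of arm with service rather than loss of power. On the plan's ICC, chance service imbalance contributes an SD of about 5 to 6 min/week, against a standard error of about 19 and a planned difference of 59.3. Power falls clearly below 0.80 only at extreme splits such as 7:2 or 10:2. This rests on three or four clinicians per service, equal cluster sizes, a two-sided test, and the full ICC of 0.005 being due to service. If the true service effect is smaller, the harm is smaller still.

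**What to change.** In the Design section, state that clinicians are randomised within strata defined by health service, after all have agreed and before the study starts, so that every service has clinicians in both arms. With three clinicians per service, stratification alone could still give 6:3, so balance the odd clinicians across services to keep the arms within one clinician of each other overall. Add health service as a fixed effect in the primary ANCOVA. Reconcile the nine clinicians implied by "three clinicians from each of the three health services" with the 12 used for the sample size. If allocation is already restricted in this way, one sentence saying so is enough.

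The cost is a different allocation list and a few lines of text, with no extra patients or staff, because clinicians are already allocated before the study starts. The downsides are two degrees of freedom for service in an analysis with few clusters, and somewhat more mixing of arms within services.

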### Participants

Eligible patients will be adult males who 1) have completed active treatment for prostate cancer within the previous three-12 months. Participants currently on hormone treatment will be eligible to participate; 2) were treated with curative intent, representing stages I, II, or III; and (3) have the ability to complete surveys in the English language. Patients will be excluded from this study if they have musculoskeletal, cardiovascular, or neurological disorders that could limit them from exercising. The patients' treating clinicians will assess their eligibility for the study.

The sample size for this study was calculated based on the primary research question; number of minutes of moderate or strenuous physical activity in a typical week in past month as measured by an adapted version of the Leisure Time Exercise Questionnaire at the completion of the 12 week intervention using the following assumptions: (1) a medium-sized effect will be found, (2) α will be set at .05, (3) power will be set at .80, (4) the attrition rate will be 10% at 12 weeks, and (5) the design effect will be 1.084. The anticipated effect size was judged from a similar project [24], where a medium-sized effect was found for the outcome of a physical activity intervention (*d *= 0.484), where the intervention group increase their total weekly minutes of physical activity by 59.3 minutes (SD = 126.6).

Physical activity levels will be measured at 12 weeks to answer the primary research question. An attrition rate of 10% is expected, based on our previous work in this area [22]. A design effect of 1.084 was included to account for clustering (ICC = .005, *m¯¬ *= 16.83). The ICC was estimated from a recently completed study investigating recruitment of newly diagnosed prostate and colorectal cancer patients (clustered by specialist) [22] and from published commentary in which the authors suggested that ICC rates of less than 0.01 have been found for practitioner prescribing rates [23]. The average size of each cluster (*m¯*) was calculated from an estimation of the number of participants needed in this study before the application of the design effect (*n *= 202) and the number of clinicians (clusters) involved in this research (*n *= 12). Based on these assumptions, 220 participants will need to be recruited.

### Physical Activity Program

Participants will initially undertake a one-on-one session with the exercise physiologist, which will involve a discussion of each participant's beliefs in his or her ability to be physically active, physical activity preferences, outcome expectations, goals, and strategies for using facilitators and overcoming barriers to performing physical activity. The topics for this discussion are based on the concepts (previously identified) within social cognitive theory that are particularly relevant to health behaviour [19,20]. This is to increase long-term adherence to physical activity.

Emphasis will be placed on exercise physiologists regularly counselling participants throughout the structured physical activity sessions. The counselling topics will be based on the constructs of social cognitive theory. Exercise physiologists involved in this study will be trained in the application of social cognitive theory to physical activity uptake and adherence for survivors of prostate cancer. Exercise physiologists will be provided with checklists to ensure that they are regularly discussing key factors, including setting goals, aligning activity with outcome expectations, overcoming barriers and drawing on facilitators.

Based on previous work with prostate cancer patients [25], participants will undertake a 12-week program that will include supervised physical activity sessions and unsupervised physical activity. During the supervised sessions, several participants may be exercising at the same time. As participants will enter and leave the program at varying times and will have different weekly schedules, no attempt will be made to allocate participants to groups that will train in 12-week blocks. The physical activity program will be tailored to suit the ability of each participant. Exercise physiologists will lead two supervised sessions per week and will advise participants on what physical activity to undertake during their one non-supervised session per week.

Each supervised session will last approximately 50 minutes and participants will be encouraged to socialise following the sessions. The goal of the exercise training is to achieve 150 minutes per week of moderate to strenuous physical activity. Following the intervention, participants will be provided with a physical activity program by the exercise physiologist. The program will be based on the preferences of the participant, in terms of setting and type of exercise. The main goal of this training will be to maintain 150 minutes per week of moderate to strenuous physical activity [26].

Supervised and unsupervised physical activity has been included as both offer unique advantages. Supervised programs have value because participants can be directly observed (which may decrease risk of injury and also improve adherence to physical activity) and unsupervised programs are beneficial because of their potential to increase long term adoption and maintenance of physical activity, especially if participants find cost effective ways to incorporate physical activity into their daily routine [27]. Combining these approaches means that participants receive guidance on physical activity techniques and principles; have regular contact with, and encouragement from, the exercise physiologists and other participants; and have opportunities to explore ways of integrating physical activity into their lives.

The content of the active exercise program was informed by Exercise Guidelines for Cancer Survivors of the American College of Sports Medicine [28] and the Australian Association for Exercise and Sport Science [29], now known as Exercise and Sports Science Australia. The general program, which will be individualised for each participant, will include three sessions per week (two supervised and one unsupervised). Each session will involve aerobic exercise, progressive resistance training, balance, and flexibility exercises. The aerobic exercise will include different modes of training (e.g., walking, jogging, cycling, cross training, rowing), for 20 minutes, at an intensity of 40% to 70% of predicted heart maximum rates or 8 to 13 on the 15-point Borg scale of perceived exertion [30,31]. Progressive resistance training exercises (two to four compound exercises for lower and upper body, one core strength exercise) will be programmed using Thera-Bands and progressing to machines and free weights. One set of 8 to 12 repetitions of each exercise will be performed in the initial session, progressing to two sets of 8 to 12 repetitions of each exercise in subsequent sessions, depending on the tolerance for exercise of each participant. In the unsupervised sessions, body weight and Thera-band exercises will be prescribed for the progressive resistance training component of the program. Balance exercises will include the one legged stand, tandem stand and walk, and one legged semi squats. Flexibility exercises will be prescribed for every major muscle group.

### Measures

Table 1 provides a summary of the constructs and their measurement for this study.

**Table 1 T1:** Constructs and Measures

Construct	Measure
**Primary Outcome**	
Participation in Physical Activity	Self-report using an adapted version of Godin and Shephard's 'Leisure Time Exercise Questionnaire' [32]
**Secondary Outcomes**	
Objective Physical Functioning	Resting heart rate, blood pressure, limb girth circumferences, 6 minute walk, sit to stand (30 seconds), 1 repetition maximum strength test, and Apley's shoulder test [43].
Accelerometer measure	The Actigraph GT3X accelerometer is a small matchbox-sized unit worn on a belt on the hip that is a valid and reliable tool for measuring physical activity among adults [45,46], and will be worn for eight consecutive days, before the intervention commences and during the final week of the intervention.
Quality of Life	European Organization for Research and Treatment of Cancer core quality of life questionnaire (EORTC QLQ-C30, version 3 [35]) and the prostate tumour-specific module (EORTC QLQ-PR25 [36]).
Anxiety	Memorial Anxiety Scale for Prostate Cancer (MAX-PC) [37]
Depression	Centre for Epidemiological Studies Depression Inventory (CES-D) [40].
**Mediators**	
Task Self-Efficacy	Participants rate the certainty with which they believe they can perform three physical tasks. For each task, they rate the certainty with which they believe they can perform these tasks for three time durations: 10, 20, and 30 minutes. Confidence will be measured on an 11-point Likert scale, from 0 (not at all confident) to 100 (extremely confident). Measure based on exercise and cancer research in which task self-efficacy was measured [48].
Barrier Self-Efficacy	Participants rate the certainty with which they believe they can perform exercise when faced with specific barriers. Items (barriers) from Bandura's [47] self-efficacy to regulate exercise instrument, with supplementary items from research on barriers to physical activity for prostate cancer survivors [8] and research on barrier self efficacy and cancer survivors [48]. The 11-point Likert scale used in the measurement of task self-efficacy will also be used to assess barrier self-efficacy.
Outcome Expectations	Multidimensional Outcome Expectations for Exercise Scale (MOEES) [49].
Goals	Participants indicate the number of days per week they intend to perform at least 30 minutes of exercise at a light, moderate or strenuous intensity now and in 12 weeks. Items adapted from previous research using social cognitive theory constructs [51].
Socio-Cultural Factors (factors facilitating or impeding participation in physical activity)	Participants asked perceptions of frequency with which each facilitator and barrier occurs using a 5-point-Likert scale anchored by 0 (never) and 4 (always). Measure based on guidelines for the development of scales to assess barriers to physical activity for cancer patients [52] and content (i.e., facilitators and impediments) drawn from our prior work with prostate cancer survivors [8].

